To investigate this question, a new smartphone alcohol intervention application was developed—Yoozan—with built‐in timers recording usage times of the different functions separately for every user. A randomized controlled trial will be conducted, where participants will use Yoozan or a control application (with restricted functionality, described in Methods) for 30 days, or will be allocated to a wait‐list control group. By analyzing usage times and the efficacy of the application in reducing the amount of alcohol consumed, the primary aim of the study is to evaluate the relationship between user engagement and intervention efficacy. The secondary aim of the study is to investigate the efficacy of the application functions by investigating the relationship between usage times of the application functions and intervention efficacy. The tertiary aim of the study is to investigate the efficacy of the intervention application compared to an active control application and to a wait‐list control group.

We hypothesize that there will be a positive correlation between engagement (reflected in usage time) and between the extent of reduction in alcohol consumption. We also hypothesize that Yoozan users will consume less alcohol at post‐intervention and 30, 60, 90, 120, 150, and 180 days follow‐up, compared to the participants in the control conditions.

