### Measures

2.4

At baseline weekly alcohol consumption, AUDIT score, motivation to change drinking habits, and sociodemographic data (age and gender) are assessed. Weekly alcohol consumption is assessed by the 7‐day Timeline Followback (e.g., see Sobell & Sobell, 1992) by users entering the consumption for each day of the previous week from a predefined list of drinks. It allows defining consumption measures that hopefully contribute better comparability between studies (Shorter et al., 2019), such as the frequency of drinking and heavy drinking (on a weekly level) and the summed consumption in standardized units. The AUDIT is a validated 10‐item screening tool developed by the World Health Organization (WHO) to assess alcohol consumption, drinking behaviors, and alcohol‐related problems. It is particularly designed for health care practitioners, but with suitable instructions, it can be self‐administered (Babor, Higgins‐Biddle, Saunders, & Monteiro, 2001). Motivation to change drinking habits is measured with the question “How important is it for you to change your drinking habits?” with five options to answer (1: not important, 5: very important).

The follow‐up questionnaires consist of the 7‐day Timeline Followback and application usability test. Subjective rating of application functions is measured at the first (30 days) follow‐up, with questions regarding the perceived effectiveness of each function helping to reach alcohol‐related goals, with five options to answer (1: very poor, 5: very helpful).

Besides the self‐administered tests, usage times of the application are recorded, and the following variables are formed: total usage, frequency (the number of usage sessions), and usage time of functions.

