### Educational application: Yoozan

3.1

The educational application, Yoozan, is a newly created smartphone application‐based intervention centered on Behavior Change Techniques (BCTs). BCTs are observable, replicable, and an irreducible component of an intervention designed to alter or redirect causal processes that regulate behavior (Michie et al., 2013). The motive during the selection of tools was to implement evidence‐based techniques to a mobile interface. Our work was not a pioneer in this respect; therefore, a relatively large body of evidence was available. The Drink Less application introduced by Garnett et al. (2016) used well‐reasoned modules in concordance with others (e.g., Attwood et al., 2017; Crane, 2017; Dulin, Gonzalez, King, Giroux, & Bacon, 2013), so we followed their work regarding the theoretical assumptions of the used functions. These are goal‐setting, self‐monitoring and feedback, action planning, normative feedback, and identity change (see Garnett et al., 2016). Based on the conclusion of Webb, Joseph, Yardly, and Michie (2010), by which the more BCTs were used in Internet‐based interventions, the more effective they were, additional functions were added to Yoozan. These are a chat room, providing peer support, evaluation of progress through achievements, and a state/mood‐activity diary. The state/mood‐activity diary was based on an extremely popular and well‐rated application, Daylio (Habitics, 2020; more than 5 million installs on Android, with an overall rate of 4.7 out of 5 based on more than 250,000 votes in 2020, Q2), the motive behind its use was twofold. On the one hand, based on the outstanding popularity of this formula, we anticipated that this tool would strengthen user engagement. Also, the state/mood‐activity data‐entry interface was developed in a way that it was only available once a user was done tracking the consumed drinks, serving as an additional motivation factor for tracking drinks. On the other hand, we assumed that tracking moods and activities might serve as valuable feedback, especially in relation to alcohol consumption.

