## RESULTS

4

The composition of our sample will be demonstrated via descriptive statistics of participants' age, gender, and baseline 7‐day Timeline Followback, AUDIT measures, and motivation to change scores. Random imbalances between the intervention and control groups will be examined using chi‐squared tests. To evaluate the efficacy of the intervention, a repeated measure one‐way between‐groups analysis of covariance (ANCOVA) will be conducted. The analysis model will be built with group allocation as the independent variable, change in alcohol consumption as the dependent variables (the difference between baseline and follow‐ups 7‐day Timeline Followback in consumed alcohol units, binge drinking occasions, and drinking frequency), and age, sex, and motivation to change as covariates. Prior to the analysis, we will make sure that the specific assumptions for normality and homogeneity of variance for the one‐way ANCOVA will be met. In situations where data is missing—for example, with participants who are lost to the 6‐month follow‐up—the mixed model approach will be used to estimate missing values.

Multilevel modeling will be used to estimate the relationship between change in alcohol consumption (consumed alcohol units, binge drinking, and drinking frequency), application usage (total usage time, usage frequency, and usage time of functions) and application usability ratings in the educational and control application groups.

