## DISCUSSION

5

This study protocol describes the design of a randomized controlled trial with the following aims: (1) evaluate the relationship between user engagement and intervention efficacy, (2) investigate the efficacy of the application functions by investigating the relationship between usage time of the application functions and intervention efficacy, and (3) investigate the efficacy of the educational application compared to an active control application and to a wait‐list control group. To the best of our knowledge, this will be the first study to take behavioral data into account in the evaluation of the effectiveness of a complex alcohol reduction application on a large sample. Crane et al. (2018) recorded usage times in a factorial design study, with no significant differences between application components. They also found that application components in combinations led to improvements in alcohol‐related outcomes (Crane et al., 2018), supporting the conclusion of Webb et al. (2010), that effectiveness increases with the number of BCTs. Zhang et al. (2016) found in their self‐report study that notifications and information sharing were the most, while psychotherapy was the least useful feature of their mobile application. Attwood et al. (2017) observed mixed feedback regarding the usefulness of the individual features, which emphasizes the heterogeneity of user needs.

With an attempt of taking the continuously growing knowledge of the field into account, we developed a mobile application, Yoozan, with a wide range of functionality: self‐monitoring and feedback; action planning; normative feedback; identity change; community support; goal setting; evaluation of progress; and mood‐diary. We assume that functions/components in a complex application will compete for usage, resulting in different usage times in an ecologically valid context. By registering usage time of functions on the single‐user level, it is possible to examine application efficacy as a function of usage habits such as usage time, usage frequency, the number of used functions, and usage time of functions. This data will serve as useful guidance for future application development, helping to specify effective functions and user behaviors associated with high efficacy.

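### The model for the primary and secondary aims, as described, relates self-selected usage to change in drinking with no baseline covariates named, so its association can be biased and should not be read as efficacy

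*Protocol article*

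**What the plan says.** The Introduction states that "the primary aim of the study is to evaluate the relationship between user engagement and intervention efficacy". The secondary aim is the efficacy of the individual functions, to be judged from their usage times. The randomised comparison of arms is the tertiary aim.

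Results (section 4) gives the engagement analysis one sentence. It opens "Multilevel modeling will be used to estimate the relationship between change in alcohol consumption" and continues, after listing three drinking outcomes, with "application usage (total usage time, usage frequency, and usage time of functions) and application usability ratings in the educational and control application groups". No baseline variable appears in it. The preceding paragraph, on the ANCOVA for the randomised comparison, does name adjustment variables: "and age, sex, and motivation to change as covariates".

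Measures (2.4) defines the usage variables as "total usage, frequency (the number of usage sessions), and usage time of functions". It also lists weekly consumption, AUDIT, motivation, age and gender as baseline data. The drink diary and the eBAC calculator are core functions of both apps (Table 1). The state/mood diary is tied to drink entry, because "it was only available once a user was done tracking the consumed drinks" (3.1). The Discussion expects the usage data to guide future development, "helping to specify effective functions and user behaviors associated with high efficacy". Its four limitations are self-report, unequal group sizes, missing follow-up and Android only.

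**The concern.** Randomisation balances the arms. It does not balance heavy and light users within an arm. Three routes can link usage to change in drinking when usage does nothing:

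- **Motivation.** More motivated participants may both use the app more and cut down more.
- **Baseline drinking.** The outcome is a change score, which correlates with its own baseline through regression to the mean. If usage also correlates with baseline drinking, usage and reduction correlate without any effect.
- **Logging.** Entering drinks is itself app use. Usage time may therefore partly reflect how much a person drinks, before or during the study.

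As described, the randomised comparison gets covariates, while the non-randomised analysis, which needs them more, has none named. At stake are the first two aims and the advice that the Discussion hopes to draw on which functions work.

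**Working it through.** **The plan's own figures.** Sample size calculation (2.3) uses d = 0.20, two-sided alpha 0.05 and 80% power. The t-test formula gives 393.4 per group, rounded up to the stated 394. The target of 4356 at 27% response gives 4356 × 0.27 / 3 = 392 responders per arm. The two app arms therefore supply 2 × 392 = 784. The article gives no figure for the engagement model.

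**Detectable correlation.** tanh[(1.96 + 0.84) / √(784 − 3)] = 0.10. A spurious correlation of about 0.10 is thus significant about 80% of the time.

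**Baseline drinking, closed form.** Let q be the correlation of usage with baseline drinking and rho that of baseline with follow-up drinking. Assume equal variances and no usage effect. Then cov(usage, reduction) = q(1 − rho) and var(reduction) = 2(1 − rho), so the spurious correlation is r = q√((1 − rho)/2). The two-sided rejection rate is about Φ(atanh(r)·√781 − 1.96).

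- q = 0.2, rho = 0.5: r = 0.2 × 0.50 = 0.10; Φ(2.80 − 1.96) = 80%
- q = 0.1, rho = 0.5: r = 0.1 × 0.50 = 0.05; Φ(1.40 − 1.96) = 29%
- q = 0.2, rho = 0.7: r = 0.2 × 0.387 = 0.077; Φ(2.17 − 1.96) = 58%
- q = 0.1, rho = 0.7: r = 0.1 × 0.387 = 0.039; Φ(1.08 − 1.96) = 19%

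A simulation of 4000 trials at q = 0.2 agreed (80% at rho 0.5, 59% at rho 0.7). Adding baseline drinking to the model brought the rate back to 5%.

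**Simulation of all three routes.** Settings: 784 responders, rho = 0.6, zero usage effect, 2000 runs per scenario, and one follow-up in a single-level regression as a simplification of the multilevel model. The same follow-up drinking value stands for drinking during use. The figures are rates of a significant benefit (nominal 2.5%) unless harm is stated.

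- No confounding: 2.4%
- Motivation acting on usage and on drinking at 0.2 SD each: 21%
- The same at 0.3 SD each: 74%
- Usage rising 0.2 SD per SD of baseline drinking: 68%
- The three confounded scenarios adjusted for motivation and baseline consumption: about 2% to 3%
- Usage rising 0.2 SD per SD of current drinking: 0% benefit and 69% significant harm unadjusted; 99% harm after adjustment
- Baseline and current drinking links both at 0.2 SD: mean correlation about 0 unadjusted, but more than 99% harm after adjustment

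Covariates therefore deal with the first two routes and not with logging of current drinking. In that scenario, adjustment alone makes the distortion more visible.

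**The case against.** The best defence is that a journal article condenses the full plan. One sentence without a list of model terms does not say that the model is unadjusted. That stands: the point is that no covariates are *named*, not that none will be used. It does not dispose of the matter, because the article spells out covariates for the ANCOVA one paragraph earlier, fixes a change score as the outcome, describes function efficacy as something to be read from usage times, and omits confounding from its limitations.

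Several stronger readings are tempting but not supported:

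- **Logging must create a false benefit.** The documents show that drink entry is app use and gates the mood diary. They do not show the size or sign of the resulting bias. Logging driven by baseline drinking inflates benefit, logging driven by current drinking suggests harm, and the two can cancel.
- **A false positive is likely.** The higher rates need assumed correlations near the top of the range shown. Weaker ones give 19% to 29%, still well above 5%.
- **Slips causing disuse contaminate every outcome.** The planned use period is 30 days, so overlap between usage and the recall week concerns mainly day 30. The outcome weeks from day 60 onward follow it.
- **Arms are pooled without an arm term, total and function times share one model, or same-day usability ratings are an error.** The text states none of these.

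The protocol also already plans the randomised Yoozan versus control-app contrast (3.5 and Results), which gives an unconfounded estimate of the effect of adding the modules. Much of its wording is already that of association.

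**Conclusion.** The point holds in limited form. As described, the analysis for the first two aims relates a change score to self-selected usage with no baseline covariates named, and its result is to be interpreted partly as the efficacy of functions. With about 784 responders, even a spurious correlation of 0.05 to 0.10 is significant in about 29% to 80% of trials. The sizes rest on assumed confounding strengths, on a baseline to follow-up correlation of 0.5 to 0.7, and on a simplified single-level model; the documents give none of these values. Logging time adds a bias of unknown direction. The conclusion is that the association cannot separate a useful function from a motivated or heavier-drinking user, not that it will necessarily show a false benefit.

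**What to change.** 1. Model follow-up consumption, rather than change, on usage, with baseline consumption, AUDIT, motivation, age, sex and arm as covariates.
2. Separate drink-entry and eBAC time from other usage and analyse it apart. Covariates do not replace this step.
3. Estimate the association for module time within the Yoozan arm only, since the control app has no modules.
4. For the day-30 outcome, use only usage from before the seven recalled days, if dated usage is available. The article documents timers, session counts and function times, but not date stamps.
5. Report the results as adjusted associations rather than efficacy of functions, and add confounding and reverse causation to the limitations. Rest claims about the modules' effect on the randomised contrast already planned.

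All the covariates are already collected, so items 1, 3 and 5 cost only wording and a little analysis. Item 2 needs the function-level times that the app records, with drink entry and eBAC identifiable among them. Item 4 depends on the stored data. The downside is more modest language about individual functions.

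### The usage model for the primary and secondary aims names no baseline covariate, so a link between app use and reduced drinking may partly or wholly reflect motivation or baseline drinking

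*Protocol article*

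**What the plan says.** The Introduction ranks the aims. It states that "the primary aim of the study is to evaluate the relationship between user engagement and intervention efficacy", and then: "The secondary aim of the study is to investigate the efficacy of the application functions", to be done by relating the usage time of each function to efficacy. The comparison of randomised arms is the tertiary aim. The first hypothesis is a positive correlation between usage time and the extent of reduction in drinking.

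Section 4 (Results) plans two analyses. The randomised comparison is an ANCOVA with group as the independent variable, change in drinking as the outcome, "and age, sex, and motivation to change as covariates". For usage, the text is one sentence: "Multilevel modeling will be used to estimate the relationship between change in alcohol consumption" (units, binge drinking, frequency), usage (total time, frequency, time by function) and usability ratings, in the educational and control app groups. No baseline variable is named there.

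Section 2.4 (Measures) shows what is available at baseline: 7-day Timeline Followback, AUDIT, age, gender, and motivation from a single five-option item ("How important is it for you to change your drinking habits"). Section 2.2 requires a motivation score of at least 2, so enrolled participants range from 2 to 5.

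The Discussion says the usage data will guide future development, "helping to specify effective functions and user behaviors associated with high efficacy". It lists four limitations. Confounding of usage is not one of them.

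**The concern.** Within the app arms, how much a person uses the app is their own choice, so randomisation does not protect this comparison. Motivation to change is a plausible common cause: a motivated person may both open the app more and cut down more. The plan already treats motivation as relevant, since it screens on it to ensure willingness to change and adjusts for it in the ANCOVA.

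Baseline drinking is a second route. It is part of the change score by construction. It may also raise usage, because heavier drinkers have more to log and, by section 3.1, the mood diary opens only after drinks have been tracked.

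The usability ratings do not stand in for these variables. They are taken at day 30, after use (Table 2).

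At stake is how the first two aims are interpreted. The hypothesised correlation could appear with no effect of use, and a function could look effective because motivated people spend time in it.

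**Working it through.** **1. The plan's own figures.** Section 2.3 uses d = 0.20, 80% power and two-sided alpha 0.05, and gives 394 per group. The two-sample t calculation gives 393.4, rounded up to 394, which agrees. At 27% response, 394 / 0.27 = 1459.3, so 1460 per arm and 4380 in total. The article states 4356, about 0.5% lower, which does not matter here. The article gives no sample size or power figure for the usage model.

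**2. Responders available to the usage model.** Allocation is equal across three arms (section 2.2). 4356 × 2/3 = 2904 app users; 2904 × 0.27 = 784 responders at the first follow-up.

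**3. Smallest correlation detectable with 80% power at that size.** tanh((1.96 + 0.842) / √(784 − 3)) = tanh(2.802 / 27.95) = 0.10. Small spurious correlations are therefore within reach of the test.

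**4. Spurious correlation through motivation.** Let a be the correlation of motivation with usage and b its correlation with reduction, with no effect of use. Then the expected correlation of usage with reduction is r = a × b. The rejection rate follows from Fisher's z, with mean arctanh(r) × √781. The article gives neither a nor b, so all values are assumptions.

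| a = b (assumed) | r | z mean | Rejection, no covariate |
|---|---|---|---|
| 0.1 | 0.01 | 0.28 | about 6% |
| 0.2 | 0.04 | 1.12 | about 20% |
| 0.3 | 0.09 | 2.52 | about 71% |

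A simulation with 3000 runs per setting gave 21% at 0.2 and 71% at 0.3. With a = 0 (b = 0.3) it gave 4.9%: if motivation is unrelated to use, it causes no bias.

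**5. Spurious correlation through baseline drinking.** With equal variances and baseline/follow-up correlation ρ, the correlation of baseline with (baseline − follow-up) is √((1 − ρ)/2), which is 0.5 at an assumed ρ = 0.5. If usage correlates 0.1 or 0.2 with baseline drinking and is otherwise unrelated to outcome, r = 0.1 × 0.5 = 0.05 or 0.2 × 0.5 = 0.10. Rejection is then about 29% or 80%. These inputs are also assumed.

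**6. What adjustment can and cannot do.** In the simulation, adjusting for motivation measured without error brought rejection to 4.5% and 4.8% at 0.2 and 0.3. With a four-level item (scores 2 to 5) carrying assumed error (SD 0.65 on a unit-variance scale), adjusted rejection stayed at 7% and 18%. Adjustment lowers the bias but does not remove it.

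Steps 3 to 6 treat one follow-up and a simple correlation or regression. They illustrate the mechanism and are not the error rate of the planned multilevel model.

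**The case against.** **The sentence does not say the model is unadjusted.** It names a relationship among three sets of measures and gives no levels, random effects or covariates. A condensed article may leave these to a fuller document. This stands in part: a reader might infer that the plan rules covariates out, and the text does not support that. But the same section does name covariates for the ANCOVA and none for the analysis that serves the first two aims. The contrast covers only age, sex and motivation, because the ANCOVA list omits AUDIT and baseline drinking too.

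**An association is all that is hypothesised.** The article mostly speaks of relationship, correlation and association. If motivation drives both use and reduction, that correlation exists and rejecting zero is correct. This stands: the rates above are errors only under a causal reading. That reading is, however, invited by the wording of the secondary aim and by the Discussion's intention to identify effective functions.

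**The sizes are assumed.** This stands. At 0.1/0.1 the rate is close to nominal, and restricting a single item to scores 2 to 5 tends to weaken its correlations.

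**The covariates are in the wrong model.** A reader might infer this from the contrast, but it is not a fair charge. Covariates in a randomised comparison improve precision, and having them in the ANCOVA is no error.

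**Conclusion.** The point holds in a limited form. As published, the model for the primary and secondary aims names none of the baseline variables that the trial collects, its exposure is self-selected, and the article means to draw conclusions about which functions are effective. A usage–reduction association could arise partly or wholly from motivation or baseline drinking.

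How large this would be cannot be known from the article. With 784 responders, a single follow-up and no effect of use, the illustrative rejection rate runs from about 6% to about 71% as the two assumed motivation correlations go from 0.1 to 0.3. The documents support saying that confounding can create the hypothesised correlation. They do not support saying that it will.

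A reader might also infer that adding the covariates restores the 5% error rate. That holds only if motivation is measured without error. With one coarse item, residual confounding is likely. Reverse causation, where people who fail to cut down stop using the app, is untouched by baseline covariates.

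**What to change.** - In section 4, add baseline motivation, AUDIT, baseline Timeline Followback consumption, age and sex to the multilevel usage model, for every usage measure. If a fuller document already does this, align the article with it.
- State there that the usage and function results are adjusted associations, that residual confounding and reverse causation remain possible, and that causal claims about efficacy rest on the randomised arms. Bring the wording of the secondary aim and the Discussion into line.
- Add confounding of self-selected usage to the limitations in section 5.

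Using randomised arm as an instrument for usage is not recommended as a substitute. The two apps differ in content and wait-list participants know they are waiting, so it is doubtful that arm acts only through amount of use.

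The cost is a few sentences, a few degrees of freedom and a more modest conclusion. No new data are needed.
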